## Methods

The protocol for this clinical trial is reported according to the SPIRIT guidelines/methodology (http://www.spirit-statement.org/wp-content/uploads/2013/01/SPIRIT-Checklist-download-8Jan13.pdf). The study was registered at Clinicaltrials.gov under registration number NCT04604665 on October 26, 2020 (Not recruiting yet, Version No 1).

### Study design

The “Pressure ulcer prevention by nursing (PENFUP phase II) study” is a pragmatic cluster randomized controlled clinical trial of parallel groups, multicenter, with a blind evaluation of outcomes for data analysts [16]. The study compares the impact of a high-frequency indication of repositioning (every 2 h) in developing pressure ulcers with conventional care in adult- intensive care units (ICU).

Eligible intensive care units from hospitals of Colombia will be randomized and allocated to perform interventions in which staff from each ICU will be in charge of applying postural shifts (repositioning) at a high frequency that is lesser than or equal to every 2 h in 24 h’ span (experimental group A) or to perform posture shifts according to conventional care (Fig. 1. PENFUP Phase 2-Flowdiagram).

**Fig. 1 Fig1:**
[figure not shown]
Consort flow diagram

### Setting

All hospitals of various regions of Colombia (north, south, central-east, and west) that have adult ICUs will be asked to partake. Hospitals will be eligible if their heads of staff, including hospital nurse director, chief nurse, and medical director in their ICU’s, accept to participate, in addition to accepting the use of usual practices that would be assigned randomly. The complete study has a duration of 36 months, and the recruitment of patients in each ICU are expected to be completed in a timeline of 3–4 months (Fig. 2).

**Fig. 2 Fig2:**
[figure not shown]
SPIRIT timeline of the study. The complete timeline of the study is about 36 months

### Inclusion and exclusion criteria

Criteria for clusters (ICUs) inclusion: ICUs that admit adult patients (≥ 18 years) in critical condition, with any type of care emphasis (surgical, medical, neurological, or a mixture of any), with a minimum of 10 beds, that submit the feasibility survey and agree to commit to the care assigned in the randomization until including the total number of the sample. At least one ICU will be included from each hospital. In case one hospital may participate with more than one ICU, the units should have to receive the same allocation resulting from the randomization.

Criteria for clusters exclusion: intermediate care units or coronary care units in which patients are self-mobilized; or critical units for burned patients. Also, units destined for the care of patients with Covid 19 in which the standard of repositioning is between every 12–16 h.

Criteria for patient inclusion in each cluster: all patients are eligible as long as they are completely unable to move, have their skin intact at the moment of their admission into the ICU, are care-dependent for their complete mobilization (including unconsciousness, being under sedation or assisted ventilation), and are scheduled for a hospitalization period of at least 48 h.

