### Sample size

Twenty-two ICUs will be included, each with a total of 150 patients in each branch of the study until completing a sample size of 3.300 patients. The calculation for this sample considered the rate of pressure ulcers observed in PENFUP phase 1 (7.5%) in the control group (patients who received preventative care with skin moisturizing) [17]. As a result of this process, it was decided that the highest incidence rate acceptable for the conventional group for repositioning would be 0.075 and that the incidence in the intervention group with high repositioning frequency would be 0.023 (2.3/7 = 0.32).

For the hypothesis of the study, we calculated a 50% low-impact reduction in pressure ulcers in ICUs that execute repositioning at a high frequency (intervention group A), compared to the ones that implement repositioning at conventional care or control group. The number of ICUs and individuals in there would be obtained by a calculation considering an intra-class correlation coefficient of 0.035 previously attained in the Chaboyer study et al. (2016), a power of 80%, and an alpha error of 0.05% resulting in a 50% difference between both intervention groups [18].

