### Randomization and blinding

Previous consent to participate will be solicited for the director of each cluster (medical director of the ICU, nursing coordinator of the ICU) and for nursing staff that will perform the intervention.

All the ICUs participants will be randomized (ratio 1:1) to be assigned to either an intervention group (an indication of repositioning every 2 h) or to conventional care (Intervention provided by care providers using a non-standardized frequency of repositioning). The randomization will be set in the main execution center of the study, which is Fundación Cardioinfantil located in Bogotá, and will be computerized with random numbers. Besides, randomization will be executed using a permutation design by blocks of two possible combinations (intervention A or B). The allocation will be openly announced in each hospital. The study will be blind to evaluators (internal analysts and statisticians) [16, 19, 20]. Furthermore, following this, we plan to apply a consent form for the patients [or their parents according to their health status] when admitted to the ICU.

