### Data collection and procedure

Various hospitals from different regions of Colombia will be recruited from a list of 60–100, each of which will be handed a feasibility survey and a prior discussion, which will help decide each hospital’s eligibility for entering the study. Any hospital that decides that the study is allowed to proceed in its facilities (depending on board matters, nurse-patient relationship, and prior consent to execute interventions resulting from randomization, approval from the medical director and nursing director with a prior protocol explanation) agrees and commits to participating in the study and executing the designated intervention. Having decided which hospitals are eligible, the study will be sent to their own board of ethics committees for careful evaluation and approval.

If this is the case and to proceed with the study, the medical director and nursing director must sign a consent form and all involved nursing staff based on the hospitals’ ethics committee demands. Patients will also be required to sign a document of informed consent to authorize the registration of relevant data regarding their health and medical record. Once each hospital is familiar with the assigned intervention**,** all involved staff will receive instructions for the study implementation and its procedures to be applied in their respective ICUs.

Each intervention will be executed by healthcare staff (nurses and nursing assistants) consecutively according to the allocated intervention in all patients until reaching the study sample in each ICU (150 patients). For ensuring the consistency of the interventions, the total of postural shifts per ICU, in all frequencies, will be recorded daily during a span of 3 months along the course of the intervention by a data collector from patient’s charts from both groups.

A patient will remain in the study from the moment of admission into the ICU until he or she is either transferred to another service or another hospital center, begins walking, or ambulation develops a pressure ulcer or dies.

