### Statistical analysis

All ICUs shall be analyzed according to the branch they were randomized to (Intention to treat) [7, 23]. The incidence of PU will be analyzed considering the time of natural first appearance; that is, within the time-lapse in which the patients are in the study. The two-time variables to be considered for this analysis will be admission into the ICU and the emergence of PUs since the time of admission for each patient. Also, we will include the length of stay in the ICU. The characteristics of the clusters and each individual will be analyzed considering counts (%), means (SD), medians (interquartile range). The percentage of applied interventions (repositioning) by clusters in each group will be computed according to the total of interventions that should be administered in both branches of high frequency and conventional care. The primary analysis will be done at the cluster level (ICU) and the secondary at an individual level (each patient). When analyzing at a cluster level, the total number of PUs will be divided by the total of accumulated days of each patient in each cluster to obtain incidence rates in both groups; this is done based on the permanence of the patients from each cluster. To calculate the incidence rate (IR of 95%), the incidence rate in the groups with a higher frequency of postural changes in group A will be divided by the control groups’ incidence rate of postural changes in group B. The incidence of PU will be analyzed considering the time of natural first appearance; that is, within the time-lapse in which the patients are in the study.

The secondary result includes evaluating the frequency of the severity of PUs (stages I - IV) and will be compared with both groups using an adjusted Chi-square test. For the individual evaluation of the risk of PUs in patients, the first PU to appear in each patient will be considered for calculating the rate of events and time before the event. The hazard ratio (HR) will be computed using Cox proportional-hazard models and its corresponding 95% confidence intervals (CI), adjusted by the standard error by cluster (SE) [23]. The Cox models will be implemented for exploring relations between the main result and the explanatory considering the time before the time of occurrence.

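### Where a hospital enters several ICUs, the shared-allocation rule makes the hospital the randomized unit, but the protocol randomizes, sizes and analyses by ICU

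*Protocol article*

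**What the plan says.** All statements are in the Methods of the protocol article.

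- **Inclusion and exclusion criteria.** The cluster is the ICU: "Criteria for clusters (ICUs) inclusion". Several ICUs per hospital are allowed: "At least one ICU will be included from each hospital". For that case there is a rule: "In case one hospital may participate with more than one ICU, the units should have to receive the same allocation resulting from the randomization".
- **Randomization and blinding.** The unit is the ICU: "All the ICUs participants will be randomized (ratio 1:1".
- **Sample size and Data collection.** "Twenty-two ICUs will be included", with recruitment continuing "until reaching the study sample in each ICU (150 patients". A single intra-class correlation of 0.035 is used.
- **Statistical analysis.** "The primary analysis will be done at the cluster level (ICU) and the secondary at an individual level (each patient". The Cox hazard ratio is "adjusted by the standard error by cluster (SE".

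No section names the hospital as a unit of randomization, of sample size or of analysis.

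**The concern.** Units that must share an allocation are not assigned separately. For a hospital with two ICUs there is one random assignment, not two, so the eligibility rule and the statement that ICUs are randomized 1:1 cannot both hold literally there.

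The mismatch matters if outcomes in such ICUs are correlated, and the text gives reason to expect some correlation. Other preventive care follows each hospital's own protocols (Control group B), and the data-collection section treats prevention protocols, nurse-to-patient relation and the previous year's ulcer incidence as hospital characteristics. An analysis that counts these ICUs as separate clusters overstates the number of independent units. That affects the primary rate ratio, the Cox hazard ratio, and the two interim looks, where a difference at the 0.05 level can end the trial.

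**Working it through.** **Inputs from the protocol.** 22 ICUs, 11 per arm at 1:1; m = 150 patients per ICU; total 3,300; ICC = 0.035; incidence 0.075 v 0.023; power 80%. Alpha is printed as 0.05% and is read here as 0.05, two-sided, because 0.0005 two-sided would need 7,992 patients.

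**Step 1: reproduce the stated sample size.**
- Comparison of two proportions, no continuity correction: 270 per arm.
- Design effect with the ICU as cluster: 1 + (150 - 1) × 0.035 = 6.215.
- 270 × 6.215 = 1,678 per arm, or 3,356 in total. This is 1.7% above 3,300.
- Power with 11 ICUs per arm: the effective size is 1,650 / 6.215 = 265.5 per arm, giving 79.4%.

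A one-sided calculation with continuity correction (3,108, which rounds up to 11 ICUs per arm) also leads to 22 ICUs, so the exact method is not certain. Both routes use the 6.215 design effect, which takes every ICU as an independent cluster.

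**Step 2: allow for shared hospitals.** Two quantities are assumptions, not in the document:
- f, the share of the 0.035 correlation that also holds between patients in different ICUs of one hospital, taken as 25% to 100%;
- q, the proportion of the 22 ICUs that have a sister ICU in the same hospital (at most two ICUs per hospital).

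Then

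DE(hospital) = 6.215 + 150 × 0.035 × f × q = 6.215 + 5.25 f q

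SE ratio (true / ICU-level) = √(DE(hospital) / 6.215)

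Actual level of a nominal 5% test = 2 × [1 - Φ(1.96 / SE ratio)]

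**Step 3: results.**

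| Scenario | q | f | DE(hospital) | SE ratio | Actual level | Power, 0.075 v 0.023 |
|---|---|---|---|---|---|---|
| 22 hospitals, one ICU each | 0 | any | 6.215 | 1.00 | 5.0% | 79.4% |
| 18 hospitals, 4 with two ICUs | 8/22 | 25% | 6.69 | 1.04 | 5.9% | 76.4% |
| | | 50% | 7.17 | 1.07 | 6.8% | 73.5% |
| | | 100% | 8.12 | 1.14 | 8.6% | 68.1% |
| 11 hospitals, two ICUs each | 1 | 25% | 7.53 | 1.10 | 7.5% | 71.4% |
| | | 50% | 8.84 | 1.19 | 10.0% | 64.4% |
| | | 100% | 11.47 | 1.36 | 14.9% | 53.3% |

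The actual level assumes analysis by ICU; the power column assumes correct analysis by hospital. For example, 4 of 18 hospitals at f = 25% gives 5.25 × 0.25 × 8/22 = 0.477, DE = 6.692, ratio √(6.692 / 6.215) = 1.038, and 1.96 / 1.038 = 1.889, which is a two-sided level of 5.9%.

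A ratio of 1.36 means that the true standard error is 36% larger. Put the other way, the ICU-level one is too small by 1 - 1/1.358 = 26%.

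One two-ICU hospital among 21 (q = 2/22, f = 50%) gives a level of 5.4%.

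**The case against.** The strongest reply is that nothing may go wrong. The shared-allocation rule covers a case that may not arise. Hospitals are to be drawn from a list of 60-100 to fill 22 ICUs, so one ICU per hospital is feasible, and then ICU and hospital coincide. Eligible ICUs may be surgical, medical, neurological or mixed, so full sharing of risk within a hospital is doubtful. With one or two two-ICU hospitals and moderate sharing the distortion is small. All of this stands. It limits the size of the point but does not remove the conflict between the sections.

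A second reply is that the article names no variance estimator for the primary rate ratio, and an ICU-level analysis could still carry a hospital effect. That is possible, and treating ICUs as independent is an inference from the definition of the cluster and the stated level of analysis. But the article fixes that level and ties the Cox standard error to the cluster, so an analyst following it would cluster by ICU.

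A reader might go further and infer that the trial's intervals will be too narrow whatever happens. The document does not support that, because the harm needs both a multi-ICU hospital and positive correlation. A reader might also object that no small-sample correction is stated for the cluster-adjusted standard error. Such detail ordinarily sits in an analysis plan, which is not shown, so it is no finding.

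**Conclusion.** The point holds in conditional form. The eligibility rule makes the hospital the unit of assignment wherever it enters more than one ICU, while randomization, sample size and both levels of analysis are written for the ICU. This is fixed by the text; it is not merely left to an analysis plan.

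The consequence ranges from nothing, with one ICU per hospital, through a modest inflation when a few hospitals enter two, to a serious one in the 11-hospital extreme, which the document does not exclude but nothing in it makes likely. The figures rest on the assumed 25-100% sharing, the assumed hospital counts, equal ICU sizes of 150 and a normal approximation for a difference in proportions. They indicate the scale of the problem for the rate ratio and the hazard ratio and are not exact for either. The power figures also take the protocol's 0.075 v 0.023. The 50% reduction in the same section is a separate inconsistency.

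**What to change.** 1. State that the hospital is the unit of randomization, and reword the randomization section so that it agrees with the shared-allocation rule. Do this before the allocation list is built; the article gives the status as not yet recruiting.
2. Cluster the primary rate-ratio analysis and the Cox standard error by hospital, with degrees of freedom taken from the number of hospitals.
3. Restate the power for the expected number of hospitals, with an explicit assumption for the correlation between ICUs of one hospital.

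The cost is a few sentences and a hospital identifier, which the trial should already hold because it collects hospital characteristics. If multi-ICU hospitals join, intervals will be somewhat wider and the stated power less favourable. If none joins, the results do not change. Restricting entry to one ICU per hospital would also remove the mismatch, but it alters recruitment and is not needed.

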### Sample size

Twenty-two ICUs will be included, each with a total of 150 patients in each branch of the study until completing a sample size of 3.300 patients. The calculation for this sample considered the rate of pressure ulcers observed in PENFUP phase 1 (7.5%) in the control group (patients who received preventative care with skin moisturizing) [17]. As a result of this process, it was decided that the highest incidence rate acceptable for the conventional group for repositioning would be 0.075 and that the incidence in the intervention group with high repositioning frequency would be 0.023 (2.3/7 = 0.32).

For the hypothesis of the study, we calculated a 50% low-impact reduction in pressure ulcers in ICUs that execute repositioning at a high frequency (intervention group A), compared to the ones that implement repositioning at conventional care or control group. The number of ICUs and individuals in there would be obtained by a calculation considering an intra-class correlation coefficient of 0.035 previously attained in the Chaboyer study et al. (2016), a power of 80%, and an alpha error of 0.05% resulting in a 50% difference between both intervention groups [18].

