**Methods:**

A nurse-applied cluster randomized controlled trial of parallel groups (two branches), in which 22 eligible ICUs (each consisting of 150 patients), will be randomized to a high-frequency level repositioning intervention or to a conventional care (control group). Patients will be followed until their exit from each cluster. The primary result of this study is originated by regarding pressure ulcers using clusters (number of first ulcers per patient, at the early stage of progression, first one acquired after admission for 1000 days). The secondary results include evaluating the risk index on the patients’ level (Hazard ratio, 95% IC) and a description of repositioning complications. Two interim analyses will be performed through the course of this study. A statistical difference between the groups < 0.05 in the main outcome, the progression of ulcers due to pressure (best or worst outcome in the experimental group), will determine whether the study should be put to a halt/determine the termination of the study.

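### The sample size claims 80% power for a 50% reduction, but 22 ICUs of 150 match 0.075 vs 0.023 (a 69% reduction); power for a true halving is about 45%

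*Protocol article*

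**What the plan says.** All the inputs are in the Sample size section of the protocol article.

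- **Control incidence.** It is taken from the phase 1 control group (7.5%), and "it was decided that the highest incidence rate acceptable for the conventional group for repositioning would be 0.075".
- **Intervention incidence.** The "incidence in the intervention group with high repositioning frequency would be 0.023 (2.3/7 = 0.32").
- **Hypothesis.** In the next paragraph, "we calculated a 50% low-impact reduction in pressure ulcers in ICUs that execute repositioning at a high frequency".
- **Calculation.** ICC 0.035, 80% power and an alpha printed as 0.05% are described as "resulting in a 50% difference between both intervention groups".
- **Size.** "Twenty-two ICUs will be included, each with a total of 150 patients in each branch of the study". The stated overall total is 3,300. The Methods paragraph of the abstract describes a trial "in which 22 eligible ICUs (each consisting of 150 patients), will be randomized".

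Randomization is 1:1, so the plan is 11 ICUs and 1,650 patients per arm.

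**The concern.** A fall from 0.075 to 0.023 is not a 50% reduction: 0.023/0.075 = 0.307, a reduction of 69%. A halving of 0.075 is 0.0375. The ratio in brackets fits neither figure, since 2.3/7 = 0.329 and 2.3/7.5 = 0.307, whereas 0.32 is printed. That slip is minor, but it adds to the doubt about which effect was used.

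The larger matter is the power statement. A reader is told that the trial has 80% power for a 50% difference. If the number of ICUs was in fact derived from 0.075 vs 0.023, power for the stated hypothesis is far lower. A non-significant result could then be read as evidence against a halving when the trial was never able to detect one reliably. The abstract's conclusion foresees use of the results in practice guidelines, so that misreading would have consequences.

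**Working it through.** **Inputs.** p1 = 0.075; p2 = 0.023 or 0.0375; m = 150 per ICU; ICC = 0.035; power 80%; 11 ICUs per arm (all from Sample size, with the 1:1 ratio from Randomization and blinding). Two assumptions are needed. The printed alpha of 0.05% is read as 0.05, and the test as two-sided, since sidedness is not stated.

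**Design effect.** 1 + (150 − 1) × 0.035 = 6.215. Effective size per arm = 1,650/6.215 = 265.5.

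**Required size.** n per arm before clustering = (1.96 + 0.842)² × [p1(1 − p1) + p2(1 − p2)]/(p1 − p2)².

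| Comparison | Reduction | n unclustered | × 6.215 | ICUs per arm |
|---|---|---|---|---|
| 0.075 vs 0.023 | 69% | 266.6 | 1,657 | 11.05 |
| 0.075 vs 0.0375 | 50% | 588.7 | 3,659 | 24.4 |

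The first row reproduces the plan: 11 ICUs and 1,650 patients per arm. The pooled-variance formula gives 11.2 and 24.5 ICUs per arm. With a t test the halving needs 26 per arm.

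**Power with 11 ICUs of 150 per arm.** Power = Φ{(p1 − p2)/√([p1(1 − p1) + p2(1 − p2)]/265.5) − 1.96}.

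- 0.075 vs 0.023: 0.052/0.01860 = 2.796; Φ(0.836) = 80%.
- 0.075 vs 0.0375: 0.0375/0.01993 = 1.881; Φ(−0.079) = 47%.

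| Method | 0.075 vs 0.023 | 0.075 vs 0.0375 |
|---|---|---|
| Normal, unpooled | 79.8% | 46.9% |
| Normal, pooled | 79.4% | 46.6% |
| t, 20 df | 76% | 43% |
| Simulation (20,000 beta-binomial trials, ICU-level t test) | 79.7% | 45.7% |

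The simulated rejection rate under no effect was 4.7%. The log risk ratio gives 44.9% for the halving.

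**What would rescue the claim.** With 3,300 patients, the largest intervention incidence detectable with 80% power is about 0.0227 (a 70% reduction). For 80% power at a halving the ICC would have to be about 0.012, not 0.035. By the normal approximation, power for a halving is 84% at ICC 0.01, 65% at 0.02 and 36% at 0.05.

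**Control rate.** For a fixed relative reduction, power falls with the control rate, so a value described as the highest acceptable sits at the favourable end. At 5%, power is 33% for a halving and 62% for a 69% reduction. At 10% and 15%, power for a halving is 59% and 79%.

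**The case against.** The strongest counter-argument is that 50% was the true target and the slip lies elsewhere. The phrase about patients in each branch could be read as 22 ICUs per arm. The Hayes–Bennett formula gives some support. With k² = 0.035 × 0.925/0.075 = 0.432, it yields 21.9 ICUs per arm for 0.075 vs 0.0375. So the documents do not prove which figure is the error, and the fix should not assume it.

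This does not save the stated power. The abstract randomizes 22 ICUs in all, and 22 × 150 = 3,300 is the printed total. If 22 per arm was intended, the plan enrols half of what it needs. On the design-effect formula 22 per arm gives about 76%. Hayes–Bennett also gives 11 per arm (10.5 rounded up) for 0.023. For a halving with 11 per arm, its variance term is 0.000463 + 0.000241 + 0.432 × (0.005625 + 0.001406) = 0.00374. Then 0.0375/√(0.00374/10) = 1.94, and Φ(1.94 − 1.96) = 49%.

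Other points on that side:

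- **Sidedness.** A one-sided test gives 59% for a halving, still far from 80%. The abstract's stopping rule looks in both directions, which favours two-sided. Alpha taken literally as 0.05% lowers power to about 5%.
- **Outcome scale.** The primary analysis compares rates per patient-day, whereas the sample size uses proportions. This is a fair caveat: no person-time figure is given, so the check can only follow the plan's own scale.
- **Control rate.** It could exceed 7.5%, because the patients are immobile and Grade I ulcers count. That stands, but even 15% does not quite reach 80% for a halving.
- **Confidence intervals.** The planned 95% intervals would show a careful reader whether a halving is excluded. They do not correct a wrong power statement.

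**Conclusion.** The point holds and must be fixed. The published size matches a 69% reduction, and the claim of 80% power for a 50% reduction is overstated by more than 30 percentage points. Power for a halving is 43% to 49% across the two-sided methods shown, so about 45%.

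This rests on ICC 0.035, 150 patients in every ICU, 22 ICUs in total, a control incidence of 0.075, a two-sided 5% test, and comparison of proportions as in the Sample size section. The section mentions no allowance for dropout, unequal cluster sizes or the two interim analyses; any of these would lower power further. The ratio slip and the control-rate sensitivity are secondary.

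**What to change.** Reconcile the Sample size section:

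1. State which effect the trial was meant to detect, and use one pair of incidences throughout.
2. Report power for both effects: 22 ICUs of 150 with ICC 0.035 give about 80% power for 0.075 vs 0.023 (69% reduction, ratio 0.31) and about 45% for a 50% reduction. Stop describing 50% as the effect detectable with 80% power at this size.
3. Correct the ratio, print alpha as 0.05 and state whether the test is one- or two-sided.
4. State that a non-significant result does not by itself exclude a halving.

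This costs protocol wording only. The power quoted for a 50% reduction becomes less favourable, and no patients are added.

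If 50% is the real target, the size has to change. At 150 per ICU that means about 25 ICUs per arm by the normal approximation (50 ICUs, 7,500 patients). Alternatively, the same 3,300 patients could be spread over more ICUs: 44 × 75 gives about 70% power and 60 × 55 about 79% (normal approximation). The protocol's list of 60–100 hospitals is a list to approach, not of committed sites, so this is an option to weigh and not part of the minimum fix.

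### The Sample size section attaches 80% power to a 50% reduction, but 22 ICUs of 150 patients give roughly 43–53% for that effect; about 80% belongs to the 69% reduction also stated there

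*Protocol article*

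**What the plan says.** All of the following is in the protocol article, mostly under Sample size.

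- Size: "Twenty-two ICUs will be included, each with a total of 150 patients", "until completing a sample size of 3.300 patients". The Abstract agrees that 22 is the trial total: "22 eligible ICUs (each consisting of 150 patients), will be randomized". Under Randomization and blinding: "All the ICUs participants will be randomized (ratio 1:1".
- Control incidence: "the highest incidence rate acceptable for the conventional group for repositioning would be 0.075".
- Intervention incidence: "the incidence in the intervention group with high repositioning frequency would be 0.023 (2.3/7 = 0.32".
- Hypothesis, in the next paragraph: "we calculated a 50% low-impact reduction in pressure ulcers in ICUs that execute repositioning at a high frequency".
- Power and alpha, together with an intra-class correlation of 0.035 taken from an earlier study: "a power of 80%, and an alpha error of 0.05% resulting in a 50% difference between both intervention groups".

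**The concern.** An intervention incidence of 0.023 against 0.075 is a reduction of 1 − 0.023/0.075 = 69%. A 50% reduction would be 0.0375. One sample size cannot give 80% power for both, and the section gives the 80% to the smaller effect.

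Stated power tells a reader what a non-significant result can mean. If the trial is believed to have 80% power for a halving when it has about an even chance or less, a neutral result may be given more weight against a halving than it can bear. The planned 95% confidence intervals limit this risk but do not correct the stated power.

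**Working it through.** **Inputs.** 11 ICUs per arm (22 in total, 1:1), m = 150, so 1,650 patients per arm; ICC = 0.035; p1 = 0.075; p2 = 0.023 or 0.0375.

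**Assumptions.** Alpha is 0.05 (printed as 0.05%) and two-sided (sidedness is not stated). The outcome is a proportion, as in the section's own inputs. The primary analysis under Statistical analysis uses rates per accumulated patient-day, for which the article gives no planning figures.

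**Design-effect method**

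- Design effect = 1 + (150 − 1) × 0.035 = 6.215.
- Effective n per arm = 1,650 / 6.215 = 265.5.
- z = (p1 − p2) / √{[p1(1 − p1) + p2(1 − p2)] / 265.5}; power = Φ(z − 1.96).

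Reproducing the plan's figure, 7.5% versus 2.3%:

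- z = 0.052 / √(0.091846 / 265.5) = 2.796, power 79.8%. With pooled variance it is 79.4%; with a noncentral t on 20 df, 75.8%.
- ICUs per arm for 80% power = (1.96 + 0.8416)² × 0.091846 / 0.052² × 6.215 / 150 = 11.05. The planned 11 per arm matches closely.

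The effect to which the text ties the 80%, 7.5% versus 3.75%:

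- z = 0.0375 / √(0.105469 / 265.5) = 1.881, power 46.9%. Pooled variance gives 46.6%; t on 20 df, 43.3%.
- ICUs per arm for 80% power = (1.96 + 0.8416)² × 0.105469 / 0.0375² × 6.215 / 150 = 24.4, so 25 per arm and 50 in total.

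**Between-cluster CV formula**

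- CV² = 0.035 × 0.925 / 0.075 = 0.4317 (CV 0.657).
- Per-cluster variance term V = [p1(1 − p1) + p2(1 − p2)] / 150 + 0.4317 × (p1² + p2²).
- Clusters per arm = 1 + (1.96 + 0.8416)² × V / (p1 − p2)².

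| Comparison | V | Clusters per arm for 80% | Power with 11 per arm |
|---|---|---|---|
| 7.5% vs 3.75% | 0.003738 | 21.9 (22) | 53.0%; 49.2% with the formula's one-cluster allowance |
| 7.5% vs 2.3% | 0.003269 | 10.5 (11) | 85.5%; 82.0% with the allowance |

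**Other attempts to recover 80% for a 50% reduction at 11 per arm.** Log risk ratio gives 44.9%, arcsine 47.7%, and one-sided 5% gives 59.1% (design effect, pooled variance). With two-sided 5%, the ICC would have to be about 0.012: 592 effective patients per arm are needed, and (1,650/592 − 1)/149 = 0.012.

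**Side figures.** 2.3/7 = 0.329 and 2.3/7.5 = 0.307. The printed 0.32 is neither, and none of these is a halving.

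**The case against.** The strongest objection concerns where the 22 came from. A reader might infer that it can only have been derived from 0.075 versus 0.023. The documents do not support that. The CV formula gives 22 clusters per arm for a 50% reduction, and the sentence on size ends with a reference to each arm. It is therefore possible that 22 per arm was calculated for the halving and then carried forward as a total. This objection stands as far as the origin of the error goes. It does not rescue the stated power. The 3,300 patients and the Abstract both fix 22 as the trial total, and 22 per arm would mean 6,600 patients.

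For the same reason, it does not follow that the 50% hypothesis should be deleted. It is the study's stated hypothesis, and replacing it with whichever effect suits the sample would fit the target to the number.

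Three further points are fair. Exact power depends on the method, so a single figure without a named method would be too precise. The 80% for the 69% reduction is itself approximate: 76% by t, 82–85% by the CV formula. And the alpha of 0.05% is evidently a misprint, since the Abstract uses 0.05 as its threshold; power calculated from the literal value would describe a design that nobody intends.

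**Conclusion.** The stated power is wrong as written. With the article's own inputs, power for a 50% reduction is about 43–47% by the design-effect method and 49–53% by the CV formula, against a stated 80%. The planned size gives about 80% (normal) or 76% (t, 20 df) for 7.5% versus 2.3% by the design-effect method.

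This rests on two-sided 5%, 11 ICUs of 150 per arm, ICC 0.035 and a binary outcome; power for the planned patient-day rate could differ. It does not show which effect size drove the calculation, nor that 22 ICUs is an unacceptable size. No unseen document can remove the conflict, because the article itself states both effect sizes and the power. The alpha and ratio slips are secondary.

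**What to change.** Keep 22 ICUs of 150 patients and reword the Sample size section along these lines:

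> With 11 ICUs of 150 patients per arm, ICC 0.035 and two-sided alpha 5%, the design-effect method gives about 80% power (about 76% with a t-test on 20 df) to detect 7.5% versus 2.3%, a 69% relative reduction. Power for a 50% reduction (7.5% versus 3.75%) is about 45–50%, depending on the method (43–47% by design effect, 49–53% by between-cluster CV).

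Remove the claim of 80% power for the 50% reduction. The 50% hypothesis may stay, with this power beside it. State that the calculation treats the outcome as a proportion. Correct alpha to 0.05 (5%) and the ratio to 2.3/7.5 = 0.31.

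This costs protocol wording, with any matching registry text, and a less favourable stated power for the halving; no patients are added. For information, 80% power for a 50% reduction would need about 25 ICUs per arm (50 in total; 7,500 patients at 150 each) by the design-effect method, or about 22 per arm (44 in total; 6,600 patients) by the CV formula.
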